#### Statistical power for outcome comparisons

With retrospective data from 251 NICUs collected over four years (2007–2010), analyses (two-sided tests) comparing Canada (10,800 admissions) with all other networks (82,800 admissions), for example, will be able to detect rate differences of 0.004 to 0.02 for a range of outcome rates (1% to 40%) with statistical power of 80% assuming 5% type I error rate. Similar analyses comparing Canada with one other network (3,200 to 30,800 admissions) will be able to detect rate differences of 0.007 to 0.03.

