#### Comparisons between networks

For the primary composite outcome, each of its components and the additional secondary outcomes, initial crude rates, and associated 95% and 99% confidence intervals will be calculated and graphically displayed using ‘caterpillar plots’ to visually identify differences between networks. To adjust for multiple baseline characteristics, standardized outcome ratios will be computed using the ‘indirect standardization’ approach. Each network’s observed rate will be compared with the expected rate based on the total sample from all other networks to identify networks with rates significantly above or below average. For each outcome, the expected number of events will be computed as the sum of predicted probabilities from a multivariable model (logistic regression or zero inflated negative binomial models based on data distribution) derived using data from all other networks with adjustment for confounders. Network standardized outcome ratios will be graphically displayed using ‘funnel’ plots with 95% and 99% prediction intervals for comparison between networks.

A global comparison, as well as pair-wise comparisons between networks, will be performed using multivariate regression models adjusted for confounders. Statistical models will employ generalized estimating equations to adjust analyses for clustering of infants within networks. In addition, hierarchical random-effects regression models will be used to allow for variation at the network and unit level. Statistical significance will be evaluated by applying a Bonferroni correction to account for multiple pair-wise comparisons.

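### The detectable differences for Canada against one other network assume an unadjusted 5% test on independent infants, but the plan judges these pairs with Bonferroni and models unit-level variation, so 80% power is not reached for the smaller networks

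*Protocol article*

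**What the plan says.** The section *Statistical power for outcome comparisons* gives two sets of detectable differences for outcome rates of 1% to 40%. Canada (10,800 admissions) against all other networks (82,800) "will be able to detect rate differences of 0.004 to 0.02", "with statistical power of 80% assuming 5% type I error rate". The next sentence carries this over to single networks: "Similar analyses comparing Canada with one other network (3,200 to 30,800 admissions") "will be able to detect rate differences of 0.007 to 0.03". The section mentions no multiplicity correction, ICC or design effect.

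The preceding section, *Comparisons between networks*, sets the decision rule: "Statistical significance will be evaluated by applying a Bonferroni correction to account for multiple pair-wise comparisons". It does not state the number of comparisons. It also plans generalized estimating equations with networks as clusters, and hierarchical models with random variation at network and unit level.

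**The concern.** The power statement describes a different test from the one planned. A Bonferroni correction makes each pair-wise test stricter than 5%, and unit-level variation makes the effective number of infants smaller than the count of admissions. Either lowers power at a given difference.

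Comparing outcomes among the networks is the first aim under *Network objectives*, and the results decide which problem areas are followed up with surveys and practice change. If the printed range is taken at face value, a non-significant result for a small network could be read as making a difference of 0.7 to 3 percentage points unlikely, when the planned test may have had close to an even chance of missing it.

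**Working it through.** **Inputs.** From the power section: 10,800 against 3,200 to 30,800 and against 82,800; two-sided 5%; 80% power; rates 1% and 40%. From Table 1, annual admissions times four: 3,200, 3,600, 6,000, 10,400, 14,000, 14,800 and 30,800 for the seven other networks. Eight networks give 8 × 7 / 2 = 28 pairs; Canada against each other network gives 7.

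**Formula.** Two-proportion test with pooled null variance, Canada as reference, rate rising by d:

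power = Φ[(d − z·s0)/s1], with s0 = √{p̄(1−p̄)(1/n1 + 1/n2)} and s1 = √{p1(1−p1)/n1 + p2(1−p2)/n2}.

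**Step 1: reproduce the printed figures** (alpha 0.05, independent infants, solved for 80% power).

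| Comparison | 1% rate | 40% rate | Printed |
|---|---|---|---|
| 10,800 vs 3,200 | 0.0062 | 0.0277 | 0.007 to 0.03 |
| 10,800 vs 82,800 | 0.0031 | 0.0141 | 0.004 to 0.02 |

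Rounded up, all four agree. The rounding leaves some slack: power at the printed values is 87% / 86% for the smallest network and 95% / 98% against all others.

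**Step 2: apply the Bonferroni level, no clustering.** The critical value z is 1.960 at 0.05, 2.690 at 0.05/7 = 0.00714 and 3.124 at 0.05/28 = 0.00179.

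Smallest network, 1% to 1.7%: p̄ = 0.0116, s0 = 0.002155, s1 = 0.002478.
- 28 pairs: (0.007 − 3.124 × 0.002155)/0.002478 = 0.11, power 54%.
- 7 pairs: (0.007 − 2.690 × 0.002155)/0.002478 = 0.49, power 69%.

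Smallest network, 40% to 43%: p̄ = 0.4069, s0 = 0.009887, s1 = 0.009941.
- 28 pairs: (0.03 − 3.124 × 0.009887)/0.009941 = −0.09, power 46%.
- 7 pairs: (0.03 − 2.690 × 0.009887)/0.009941 = 0.34, power 63%.

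The differences detectable with 80% power are then 0.009 / 0.039 (28 pairs) or 0.008 / 0.035 (7 pairs).

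Power at 0.007 / 0.03 for each of Canada's comparisons:

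| Other network | 7 pairs | 28 pairs |
|---|---|---|
| 3,200 | 69% / 63% | 54% / 46% |
| 3,600 | 73% / 68% | 59% / 52% |
| 6,000 | 87% / 86% | 77% / 75% |
| 10,400 | 96% / 96% | 90% / 90% |
| 14,000 to 30,800 | at least 98% | at least 94% |

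**Step 3: add clustering within units.** Table 1 sums to 23,400 admissions a year, so 93,600 over four years; 93,600 / 251 NICUs = 373 per unit. Design effect = 1 + 372 × ICC, and each group size is divided by it. The ICC is an assumption, because the article gives none. At alpha 0.05:

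| Assumed ICC | Design effect | 10,800 vs 3,200, power at 0.007 / 0.03 | 10,800 vs 82,800, power at 0.004 / 0.02 |
|---|---|---|---|
| 0.001 | 1.37 | 76% / 74% | 85% / 92% |
| 0.005 | 2.86 | 49% / 44% | 52% / 65% |
| 0.01 | 4.72 | 34% / 29% | 32% / 45% |

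Using each network's own cluster size from Table 1 (about 360 for Canada, 356 for the smallest network) changes the smallest-network column by about one point. The rounding slack from step 1 is used up at an ICC of about 0.0005 to 0.0006. With 28 pairs as well, power for the smallest network at ICC 0.001 is 38% / 30%.

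**The case against.** **The power section declares its basis.** It says 5%, and on that basis its figures are right and slightly conservative. This stands: a reader might infer a calculation error, and the documents do not support that. The fault is the mismatch with the analysis section.

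**The divisor is not stated.** Twenty-eight is the natural count for eight networks, but seven is possible for an example built around Canada. This stands, so both are shown; neither restores 80% for the smallest network in the rising-rate case. A simpler formula using only the null variance, at 0.05/7 with ordinary rounding, gives 0.0036, 0.0177, 0.0071 and 0.0348, which also round to the printed values. The printed figures therefore do not by themselves prove an unadjusted test. But the article states 5% and no divisor, so that is not its documented basis, and 28 pairs or clustering would still be uncovered.

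**The shortfall is not general.** A reader might infer that the stated power fails for every comparison. It does not. Under Bonferroni alone, networks of 10,400 or more keep at least 90%. A 1% rate that falls by 0.007 keeps 82% at 3,200 with 28 pairs. Canada against all others is not a network pair, so the pair-wise correction does not clearly reach it.

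**The clustering loss rests on an undocumented ICC.** This stands. The relevant value is the residual unit variation after case-mix adjustment, which is unknown. At ICC 0.001 the comparison with all others still has 85% / 92%. Clustering by network in the estimating equations gives no usable design effect for a contrast between networks; the unit-level model is what matters. An article may leave ICC detail to a fuller plan, but the Bonferroni shortfall needs no ICC.

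**The sample is fixed and retrospective, and interval estimates are planned.** This limits the consequence to interpretation. Nothing in the article says that non-significant pairs will be read as showing equivalence.

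**Conclusion.** The point holds for Canada against one other network. The printed range of 0.007 to 0.03 is set by the smallest network, and under the plan's own Bonferroni rule power there is about 54% / 46% (28 pairs) or 69% / 63% (7 pairs) instead of 80%. With 28 pairs, three of Canada's seven comparisons miss 80%; with 7 pairs, two do.

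These results assume a pooled two-proportion test, a rising rate, Canada as reference and independent infants. With the smaller network as reference, the 28-pair figures are 37% / 46%. Independence is inferred from the reproduction and the absence of any design effect; the article does not state it.

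Clustering lowers power further for both lines, but its size is conditional on the assumed ICC. For Canada against all others it is the only source of loss: small at ICC 0.001, below 80% at 0.005. Confidence is high on the Bonferroni mismatch and lower on the size of the clustering loss.

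**What to change.** In *Statistical power for outcome comparisons*:

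- Restate the line for Canada against one other network at the Bonferroni level, naming the number of comparisons. Before clustering this is about 0.009 to 0.039 for 28 pairs, or 0.008 to 0.035 for 7, at the smallest network.
- Give both lines over an assumed ICC range that includes small values, or from the ICC observed among the NICUs in the 2007 to 2010 data. On the assumptions above, Canada against all others would read about 0.004 to 0.017 at ICC 0.001 and 0.006 to 0.024 at 0.005.
- State the number of comparisons in *Comparisons between networks* too, so that the two sections agree.

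Holm's step-down procedure could replace Bonferroni. It controls the same family-wise error and is never less powerful, but it is optional and does not correct the power statement.

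The cost is text only. No further infants or data are needed, and the stated figures become less favourable.

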### Association of site characteristics and practices with outcomes

To identify factors contributing to outcome variation between networks, detailed information will be obtained on health service provision, including units’ physical layout, environmental characteristics, human factors, and management practices at the national and site level. The type of data and strategy for collecting this information will be determined following the comparison of outcomes between networks to target identified problem areas and evaluate the culture, context, and practices of each network. Factors with possible impact on outcome differences between and within networks will be ascertained using a variety of tools, such as surveys, recurring questionnaires, and in specific instances, site visits to explore details if permitted.

The data will be pooled across sites and networks, and statistical analyses will identify factors significantly associated with outcomes. Through a collaborative process, findings will be discussed with members of participating networks to select physical and environmental factors, human and resource factors, or processes of care that can be modified through a quality improvement process. Each network will then implement practice changes within these three main target areas according to their outcome priorities and the constraints of their respective health care systems.

#### Physical and environmental factors

For preterm infants, adaptation to the environment is crucial for their survival, wellbeing, and development. The physical environment of the NICU is significantly different from the in-utero environment and contains a wide range of sensory stimuli that a preterm infant would not be exposed to if carried to term [47]. There has been wide debate as to the optimal physical characteristics of a NICU in relation to outcomes for VLBW infants. Several units that have implemented a single infant per room design in place of the more traditional open multi-patient rooms have reported improvements in outcomes, but impact on staff satisfaction and work-efficiency remains unclear [48,49]. Higher physical demands and workloads placed on nurses could negatively affect the level of care provided. Additional key physical characteristics include internal and external noise [50,51], temperature control, exposure to light [52,53], practice of developmentally supportive care [54], provision and extent of family-centered care, provision and extent of breastfeeding support, potential for continuous parental involvement, as well as training and preparation for discharge home.

Physical characteristics will be assessed by conducting a snapshot survey of units within the iNeo networks. The survey will be developed, piloted, and implemented in collaboration with the iNeo Scientific Advisory Committee by iNeo researchers with experience investigating the extraneous factors that may impact quality of care.

#### Human and resource factors

Human factors and available resources represent another aspect of care provision possibly associated with differences in outcomes. However, associations between human and resource factors and neonatal outcomes have not been thoroughly investigated, particularly not on a national scale. Human factors include staffing in relation to day and night shifts [33,55], weekdays versus weekends [56], ratio of nurses to patients [57], pattern of work for medical and nursing staff (hours on call, total duration of active duty time over 4 week period, etc.), number and types of trainee doctors, allied healthcare personnel coverage, constitution of attending team for high-risk births, and relative expertise of the health care providers attending resuscitation of extremely preterm infants considering their overall experience in direct patient care, training, and research.

Neonatal outcomes are also impacted by resource availability and utilization, specifically volume and capacity. Units with high volume are reported to have better outcomes compared with units with low volume, possibly due to relatively increased staff experience [58,59]; however, it has also been noted that low volume units may be less crowded and have reduced rates of complications [60]. Alternatively, these differences may be secondary to centralization of care rather than volume, as seen in data from Finland [61]. Similarly, units functioning at >90% capacity at all times, irrespective of volume, may have different outcomes compared with units operating at lower capacity.

Data on human factors and resource utilization will be collected using snapshot surveys administered at the unit level. Due to likely variations from year to year, data on human factors and resource utilization will be collected on an annual basis using electronic tools (such as recurring auto-filled surveys based on previous responses so as to only report changes), and while the data may not capture variation in the daily activity levels or acuity in the unit, this will represent the average condition.

#### Care-provision factors

Clinical practices represent the third and possibly most important set of characteristics that likely contribute to variation in outcomes. Variations in clinical practices are well known among neonatal communities [8]; however, no systematic prospective approach has determined, compared, and benchmarked variations associated with outcomes. Some of the key practice variations between centers and networks include referral practices (inborn vs. outborn) [62-64], differential use of the type of initial respiratory support [65-67], types and timings of surfactant administration [68], fluid management [69], timing of initiation of parenteral nutrition [70], use of donor milk, management of patent ductus arteriosus [71], availability and use of echocardiography, use of prophylactic interventions [72] (e.g., probiotics, high frequency oscillatory ventilation, phototherapy, and L-arginine), and the scope of involvement of parents.

Specific to each secondary outcome we will identify ‘top’ performing networks and networks with significant room for improvement. Subsequently, working groups of interested stakeholders from each network will be formed to determine methods to identify possible care provision practices related to such variations. Study methods will be similar to those described earlier, and will include annual snapshot surveys of each unit, detailed questionnaires specific to practices (e.g. parental presence, use of donor milk, diagnosis and management of hypotension, etc.), and in certain instances of outstanding success, a site visit with structured exploration of the practices in question. All methods of exploration will be conducted with directions from the iNeo Governing Board and Scientific Advisory Committee to protect privacy and confidentiality. Because individual unit information will not be disclosed to the iNeo Coordinating Centre, individual networks will be asked to identify willing members for such participation.

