Even for those neonatal networks where continued improvements in outcomes have been reported, there remains significant variation within and between networks. For example, several comparative studies have identified differences in mortality rates in neonates from separate networks, regions, or countries [20-27]. In one such study, Draper et al. reported that among 10 European regions, the overall survival rate for VPT infants varied from 74.8% to 93.2% [21]. More recently, in 2012 population data from the UKNC showed a greater than three-fold variation between regional networks in the percentage (range 4.7% to 16.6%) of infants born at <30 weeks gestation and admitted to neonatal units who died at ≤28 days of age [27]. Comparison of selected Australian and Scottish neonatal intensive care units (NICUs) detected a lower risk-adjusted mortality rate for VPT/VLBW infants in Australia compared with Scotland [28].

However, studies of a single or small group of sites are subject to selection bias, which can lead to erroneous conclusions when the results are generalized to the larger population. Furthermore, comparisons of mortality alone may be misleading as mortality may be declining at the cost of increasing morbidities. Measurement of mortality as an indicator of care is also a contentious issue as there are marked variations in practice between countries including initiation or withholding of resuscitation at earlier gestational ages [29]. Thus, this protocol for the International Network for Evaluating Outcomes of Neonates (iNeo) was developed to examine neonatal morbidities in conjunction with mortality using population-based data, and assess variations in practice that impact outcomes between and within countries.

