### Rationale

Over the past 5 years, collaborations have been initiated between the CNN, NRNJ, ANZNN, and SNQ. The first ever population-based retrospective comparison between countries showed that a composite outcome of mortality or any major morbidity (bronchopulmonary dysplasia [BPD], severe neurological injury, ≥stage 3 retinopathy of prematurity [ROP], nosocomial infection [NI], and ≥ stage 2 necrotizing enterocolitis [NEC]) was lower in VLBW infants in Japan compared with Canada. In-depth analyses revealed higher rates of severe neurological injury, NEC, and NI among NICUs in the CNN, whereas rates of BPD and ROP were higher in NRNJ NICUs [30]. Comparisons between the CNN and the ANZNN for VPT infants identified that while there was no difference in mortality, the ANZNN had significantly lower rates of severe neurological injuries, ROP, NEC, and BPD, but higher rates of early onset sepsis and air leaks and longer mean length of stay [31,32]. Our latest comparisons indicated that rates of adverse outcomes at each gestational age were lower in Sweden compared with Canada (unpublished data).

Differences in the outcomes of VLBW and VPT infants between Canada and other countries could be due to any number of factors including differences in population characteristics, severity of illness, processes of care, or delivery of health care. Informal discussion has confirmed wide variations in these factors between networks. For example, compared with Canada, the use of non-invasive respiratory support is higher in Europe, the use of breast milk is higher in Japan and Scandinavia, and the use of echocardiography by neonatologists for hemodynamic monitoring is routine in Japan. Differences in the type of intervention and process of administration may underlie at least some of the variations in outcomes. In addition, there are extreme variations in health services delivery and receipt. For example, the number of outborn, very preterm infants is significantly lower in the ANZNN compared with the CNN [32]; the use of respiratory therapists is practically non-existent in European countries, whereas they play a prominent role in North American institutions; and shift work is more prevalent among junior doctors in Europe and Australia [33] compared with Canada.

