### Comparisons of neonatal outcomes between networks

#### Outcomes

The primary outcome for comparison between the networks will be a composite indicator of mortality or any of the four major neonatal morbidities (severe neurological injury, severe ROP, NEC, and BPD). Mortality will be defined as death due to any cause prior to discharge home. Severe neurological injury will be defined as ≥ stage 3 intraventricular hemorrhage (IVH) with ventricular dilatation according to the criteria of Papile et al. [38], or parenchymal injury (including periventricular leukomalacia) with or without IVH. Severe ROP will be defined as ≥ stage 3 according to the International Classification [39], or need for laser surgery or intraocular injections of anti-vascular endothelial growth factor agents. NEC will be defined as ≥ stage 2 according to Bell’s criteria [40] and BPD as oxygen requirement at 36 weeks post-menstrual age [41].

Secondary outcomes to be compared among iNeo member networks will include the individual morbidities of the composite outcome, as well as nosocomial infection defined as culture-proven sepsis (blood or cerebrospinal fluid positive for pathogenic organism) at >3 days or 72 hours postnatal age [42], patent ductus arteriosus requiring pharmacological treatment and/or surgical ligation, receipt of delivery room cardiopulmonary resuscitation, air leak syndrome, and resource utilization (length of stay and length of respiratory support). To account for potential differences in practices regarding discharge home and transfer to Level 2 community units, additional analyses will compare mortality by Day 28 after birth. All outcomes will be expressed as ratios with the denominator equal to all admissions to participating NICUs.

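### Top-performing networks are identified one secondary outcome at a time, with all admissions as denominator and no link to mortality, so a higher-mortality network can look better on BPD or length of stay

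*Protocol article*

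**What the plan says.** Care-provision factors sets the selection step: "Specific to each secondary outcome we will identify" the networks that perform best and those with much to improve. Working groups, practice questionnaires and, for outstanding success, site visits follow from it.

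The outcomes it draws on are defined under Outcomes. The primary outcome is "a composite indicator of mortality or any of the four major neonatal morbidities". Death enters as part of that composite: "Mortality will be defined as death due to any cause prior to discharge home". The secondary list carries the morbidities forward: "Secondary outcomes to be compared among iNeo member networks will include the individual morbidities of the composite outcome". It then adds nosocomial infection, treated patent ductus arteriosus, delivery room resuscitation, air leak, length of stay and length of respiratory support. Death by Day 28 is an additional analysis, introduced to deal with differences in discharge and transfer. BPD is assessed at 36 weeks post-menstrual age. The denominator for every outcome is all admissions.

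Comparisons between networks gives crude rates for the composite, each of its components and the other secondary outcomes, and standardized ratios with funnel plots for each outcome. Death before discharge is therefore compared in its own right. The Background states the overall aim: iNeo was "developed to examine neonatal morbidities in conjunction with mortality using population-based data".

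**The concern.** Death competes with most of the secondary outcomes. An infant who dies before a morbidity can be assessed stays in the denominator and cannot be a case. An infant who dies early also contributes a short stay and short respiratory support. Other things equal, higher mortality lowers all of these figures. A network could then be called top on BPD or on length of stay partly because more of its infants die, and a network that keeps more infants alive could be marked as lagging.

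The Background warns that mortality read alone can mislead, because it may fall while morbidity rises. Ranking on one morbidity alone carries the mirror-image risk. The composite protects against it, but the selection step does not use the composite. At stake is where the working groups, questionnaires and site visits are directed.

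**Working it through.** The plan states no figure for this effect, so there is none to reproduce. The check isolates the effect of death by holding case mix and BPD among survivors equal in two networks.

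**Inputs from the article (Background)**
- Death by 28 days across UK regional networks, infants born before 30 weeks: 4.7% to 16.6%. Day 28 falls before 34 weeks post-menstrual age for these infants, so all such deaths precede the 36-week BPD assessment.
- Survival of very preterm infants across ten European regions: 74.8% to 93.2%, that is, mortality of 25.2% to 6.8%.

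**Assumptions (the article gives no figures)**
- BPD among survivors, b: 25%, ranged from 15% to 40%.
- Deaths occur before BPD can be assessed.
- Mean stay: 60 days in survivors, 10 days in infants who die.

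**BPD per admission** = b × (1 − m), with m the mortality. **Death or BPD** = m + b × (1 − m).

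| Mortality m | BPD per admission, b = 25% | Death or BPD |
|---|---|---|
| 4.7% | 0.25 × 0.953 = 23.8% | 0.047 + 0.238 = 28.5% |
| 16.6% | 0.25 × 0.834 = 20.9% | 0.166 + 0.2085 = 37.5% |
| 6.8% | 0.25 × 0.932 = 23.3% | 0.068 + 0.233 = 30.1% |
| 25.2% | 0.25 × 0.748 = 18.7% | 0.252 + 0.187 = 43.9% |

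In each pair the higher-mortality network looks better on BPD and is worse on death or BPD.

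**Range over b.** For 4.7% against 16.6%, the false advantage runs from 14.3% − 12.5% = 0.018 (b = 15%) to 38.1% − 33.4% = 0.048 (b = 40%), from unrounded rates. For 6.8% against 25.2% it runs from 0.028 to 0.074. As a yardstick, Statistical power for outcome comparisons gives detectable differences of 0.007 to 0.03 for Canada against one other network. An artefact of this size could therefore be declared significant, before any allowance for clustering or the Bonferroni correction.

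**Margin.** The higher-mortality network could have BPD among survivors 0.953/0.834 = 1.14 times as high (0.932/0.748 = 1.25 times for the second pair) and still look no worse per admission.

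**Risk adjustment.** The expected count comes from a model fitted to the other networks on baseline characteristics. With equal case mix, and all other networks at 4.7% mortality, the expected BPD rate for the network at 16.6% is 23.8% and the observed rate is 20.9%. Its standardized ratio is 0.834/0.953 = 0.88. Baseline adjustment leaves the artefact in place because death comes after baseline.

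**Length of stay** = 60 × (1 − m) + 10 × m.
- m = 4.7%: 57.18 + 0.47 = 57.65 days; m = 16.6%: 50.04 + 1.66 = 51.7 days.
- m = 6.8%: 55.92 + 0.68 = 56.6 days; m = 25.2%: 44.88 + 2.52 = 47.4 days.

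**Would a survivor denominator cure it?** Under equal b the networks tie at 25%. If the extra survivors are at higher risk, they do not. Assume mortality of 8% and 14%, 25% BPD in the 86% who survive in either network, and 80% in the extra 6%. BPD per survivor is (0.215 + 0.06 × 0.80)/0.92 = 0.263/0.92 = 28.6% against 0.215/0.86 = 25.0%. Death or BPD is 0.08 + 0.263 = 34.3% against 0.14 + 0.215 = 35.5%. Whether the denominator alone helps therefore depends on who the extra survivors are.

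**The case against.** The strongest reply is that mortality is not ignored. It is compared between networks as a component of the composite, with its own standardized ratio, and again at Day 28, so a reader will have it beside every morbidity result. The secondary list is also worded as inclusive, so mortality may not be strictly outside it. This stands, and it limits the point: the gap is the missing link to the naming step.

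Second, naming a network starts an exploration and does not lead directly to adoption. Adjusted patient-level models, review of published evidence, local baseline data and safety monitoring come before or after any change. This also stands. A reader might infer that the practices of a high-mortality network would simply be copied elsewhere; the document does not support that. These later steps do not, however, alter how top networks are chosen, and the article specifies no handling of death in the association models.

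Third, a reader might take the Japan–Canada result under Rationale as proof: the composite was lower in Japan "whereas rates of BPD and ROP were higher in NRNJ NICUs". It is not proof. The article does not say that mortality was lower in Japan, and severe neurological injury, NEC and nosocomial infection were all higher in Canada, which could account for the composite. The result shows only that composite and single-morbidity rankings can disagree.

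Fourth, a condensed article may leave detailed criteria to a fuller document. That would excuse a missing threshold. Here the article states the basis of selection itself, one outcome at a time, and that basis is what needs qualifying.

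**Conclusion.** The point holds as a weakness in how networks are identified. Selection on each secondary outcome alone, with all admissions as denominator, lets early death improve a network's standing on BPD, on other morbidities that appear late, and on the two duration outcomes. Baseline adjustment does not correct this, and it sits poorly with the stated aim of reading morbidity together with mortality.

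The size is unknown. The illustrated false advantage of 0.018 to 0.074 in BPD per admission rests on regional mortality ranges, an assumed BPD rate among survivors and deaths that precede assessment. National networks may differ less in mortality, and deaths after a BPD diagnosis or after a long stay would shrink or reverse the effect. Where mortality is similar, as the article reports for Canada against Australia and New Zealand, the problem does not arise. The documents support a possible misranking that is cheap to prevent. They do not show that any named network has been or will be misranked.

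**What to change.** Amend Care-provision factors in three respects.

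1. Identify networks on each morbidity by reading its standardized ratio together with the standardized ratios for death before discharge and for death or that morbidity.
2. Do not label a network top on a morbidity when its mortality ratio is flagged as high on the funnel plot described under Comparisons between networks. That plot carries 95% and 99% limits, so state which applies.
3. Report length of stay and length of respiratory support in infants discharged alive, beside mortality, and do not use either alone to name top networks. Restricting to survivors is itself a selection, which is why mortality must be shown with it.

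Death or morbidity should be read alongside the other ratios and not serve as a pass mark. For a rare morbidity it consists mostly of mortality and says little about the morbidity itself.

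The cost is a change of wording and a few extra ratios from data already in the minimum dataset. The downside is that fewer networks may be labelled top on a given outcome.
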